### Data Analyses

#### Sample Size

The sample size was calculated to detect a difference between trial arms dependent on the frequency of PrEP adherence in the SOC arm of the cohort. Prior data from our PrEP in pregnancy studies indicate that the frequency of detectable PrEP drug levels is approximately 50% among pregnant women who initiate PrEP in MCH clinics within fully programmatic settings [12]. Since this study will exclusively enroll women who initiate PrEP in MCH, we anticipate that adherence will be similar or slightly higher. Assuming a PrEP adherence estimate of 50% in the SOC arm at 6 months post partum and a sample size of 600 (randomized 1:1), we will have 80% power to detect a minimum detectable difference of 12% between arms in PrEP adherence in the mWACh arm, assuming 15% attrition and a 2-sided test with a Cronbach α of .05 (Table S2 in Multimedia Appendix 1).

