PrEP provision to pregnant and breastfeeding women may prevent primary maternal HIV infections and help eliminate vertical HIV transmission globally. Kenya is a world leader in PrEP implementation for pregnant and postpartum women within maternal and child health (MCH) settings [7,8]. In a study integrating PrEP delivery within antenatal care (ANC) [9], most pregnant Kenyan women at risk of HIV acquisition accepted PrEP when offered during ANC [8]. However, >50% of pregnant women discontinued PrEP within 30 days of initiation [8]. Compared to nonpregnant women, pregnant women more frequently reported side effects, which often overlap with common pregnancy symptoms, as a reason for discontinuing PrEP [8,10,11] and less frequently had detectable tenofovir diphosphate (TFV-DP) levels in dried blood spots (DBS) collected at follow-up visits (52% vs 70%) [12], suggesting suboptimal adherence. Studies among women living with HIV found that motivation for antiretroviral therapy (ART) adherence wanes after breastfeeding cessation when the risk of vertical transmission diminishes [13-15]. In qualitative studies, women's reported motivation for PrEP in pregnancy was driven by the desire to have an infant who is HIV negative [10,11]. Postpartum PrEP adherence may be reduced if a mother perceives the medication is only beneficial to her infant, similar to ART adherence patterns among postpartum women living with HIV [13-15]. Moreover, remembering to take PrEP pills may be difficult with the additional demands of newborn care [16]. PrEP effectiveness depends on adherence [17-19]; therefore, PrEP programs must now focus on improving prevention-effective adherence to maximize reductions in HIV incidence [12].

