Mobile health (mHealth) technologies for public health have enormous potential to support HIV prevention and adherence among at-risk populations [20-22], including in Kenya, where cell phone ownership among women is very high at ~90% [23]. SMS text messaging–based interventions have demonstrated effectiveness in increasing adherence to ART among people living with HIV [24-27] and better treatment outcomes among women living with HIV during the peripartum period [28]. More recently, the role of SMS text message–based strategies in supporting PrEP adherence has been investigated among men who have sex with men and transgender women in the United States [29,30]. SMS text message interventions have the potential to improve PrEP adherence and could be used to address issues faced by women using PrEP via real-time texting with a health worker [31-35].

Our team developed a bidirectional communication platform, Mobile Solutions for Women’s and Children’s Health (mWACh), utilizing two-way SMS text messaging between patients and remote nurses to support ART adherence and MCH among peripartum women [36]. The mWACh intervention was feasible, acceptable, and effective at improving selected ANC outcomes, including improving ART adherence among pregnant women initiated on ART and maternal and infant birth outcomes and adherence to contraceptives [37-39]. We adapted mWACh to send PrEP-tailored, Information-Motivation-Behavioral Skills (IMB) Model–based SMS text messages to facilitate adherence among pregnant women who initiated PrEP. In a nonrandomized pre- and posttest pilot, mWACh-PrEP recipients were more likely to persist with PrEP use (42% vs 22%) and to self-report high adherence (73% missed <1 pill/week vs 55%) [31]. Nurses adequately addressed issues raised by participants on PrEP use and side effects via text message.

It is essential to develop PrEP adherence strategies for pregnant women that address PrEP side effects that may overlap with pregnancy symptoms and enhance support for adherence when peripartum life events and health issues pose challenges to sustained PrEP adherence. Therefore, we are conducting a randomized controlled trial (RCT) to determine the effect of mWACh-PrEP on PrEP adherence during pregnancy and the postpartum period.

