#### Statistical Methods and Analyses

The primary outcome, PrEP adherence at 6 months post partum, will be assessed in an intention-to-treat analysis comparing randomization arms mWACh-PrEP versus SOC. Enrollment characteristics will be compared between randomization arms to assess the balance between arms and control for any imbalanced factors. Based on a previous study of directly observed dosing conditions, we will use a hair TFV concentration cutoff of 0.038 ng/mg (corresponding to 7 doses/week) as the threshold of detection for the primary adherence outcome measured at 6 months post partum (detectable/nondetectable binary outcome) [52]. Protective PrEP drug level thresholds for cisgender women have not been established; however, current WHO and Kenyan national guidelines recommend daily (7 doses/week) oral PrEP for cisgender women. A log-binomial regression model will be used to estimate the relative risk, adjusting for any imbalances in baseline demographic, clinical, or behavioral characteristics between arms. Missing primary outcomes or loss to follow-up will be assumed nonadherent. To evaluate the sustained effect of mWACh-PrEP on PrEP-taking habits after the SMS text messaging intervention ends, the same model will be used to analyze our secondary outcome of PrEP adherence at 9 months post partum (3 months after cessation of mWACh-PrEP messaging).

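### The 50% control rate behind the sample size describes any detectable drug during pregnancy, not the daily-dosing hair outcome at 6 months post partum, and the attrition allowance does not match the missing-data rule

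*Protocol article*

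**What the plan says.** The Sample Size section cites prior data that "the frequency of detectable PrEP drug levels is approximately 50% among pregnant women who initiate PrEP in MCH clinics within fully programmatic settings". It expects adherence in this trial to be about the same or a little better, because every participant starts PrEP in a maternal and child health (MCH) clinic. Its planning input is a 50% standard-of-care rate at 6 months post partum with 600 women in two equal arms. The sensitivity it claims from this is: "we will have 80% power to detect a minimum detectable difference of 12% between arms in PrEP adherence in the mWACh arm". Dropout is set at 15%, and the test is two-sided at 0.05 (the text attaches the wrong name to this alpha; it is read here as the type I error). The section refers to Table S2, which is not shown.

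The Background section describes the same cited source as detectable tenofovir diphosphate "levels in dried blood spots (DBS) collected at follow-up visits (52% vs 70" percent; 52% is the figure for pregnant women.

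For the primary outcome, Statistical Methods and Analyses states "we will use a hair TFV concentration cutoff of 0.038 ng/mg (corresponding to 7 doses/week"), measured at 6 months post partum. The analysis is by intention to treat, missing outcomes count as nonadherent, and a log-binomial model estimates a relative risk.

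The Background section also reports that ">50% of pregnant women discontinued PrEP within 30 days of initiation" and, from a nonrandomized pilot, that "mWACh-PrEP recipients were more likely to persist with PrEP use (42% vs 22" percent).

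**The concern.** The planning rate and the endpoint differ in four ways:

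- **Threshold:** any detectable drug, against a level matched to daily dosing.
- **Period:** pregnancy, against 6 months post partum.
- **Specimen:** dried blood spots, against hair.
- **Denominator:** women who gave a sample at a follow-up visit (as the Background wording suggests), against all randomized women with missing counted as failures.

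Statistical Methods and Analyses calls the cutoff a detection threshold, which makes the two measures sound alike. The same sentence ties that cutoff to 7 doses per week, a much higher bar than any detectable drug.

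The one argument offered for carrying 50% across is that participants start PrEP in MCH clinics. The source figure already describes such women, so the argument adds nothing.

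At stake is how the result will be read. The paragraph tells readers what effect the trial can detect. If the true control rate is well below 50%, a 12-point gain is a larger proportional improvement than 50% to 62% suggests, and a null result could be over-read. The paragraph also removes 15% for attrition although the analysis keeps those women as failures, so the quoted power does not describe the planned analysis.

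**Working it through.** **Inputs.** From Sample Size: 600 women randomized 1:1 (300 per arm), 15% attrition (300 × 0.85 = 255 per arm), two-sided 0.05, 50% versus 62%. From Statistical Methods and Analyses: missing counts as nonadherent. Lower control rates are assumptions; the documents give none for this endpoint.

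**Formula.** Two-proportion normal approximation with pooled null variance, p̄ = (p1 + p2)/2:

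power = Φ{ [ |p2 − p1| − 1.96·√(2p̄(1 − p̄)/n) ] / √([p1(1 − p1) + p2(1 − p2)]/n) }

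**Step 1: the plan's own figure.** With n = 255 and p̄ = 0.56: (0.12 − 1.96 × 0.04396)/0.04364 = 0.775, so power is 78.1%. The difference detectable with 80% power is 12.3 points. The stated 80% and 12 points therefore reproduce to rounding; the arithmetic is sound from its inputs. With all 300 per arm, power is 84.3%.

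**Step 2: lower control rates.** The ratio implied by the planned rates is 62/50 = 1.24.

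| Control rate (assumed) | Power for +12 points, 255/arm | Power for +12 points, 300/arm | Ratio implied by +12 points | Power for ratio 1.24, 300/arm |
|---|---|---|---|---|
| 50% | 78.1% | 84.3% | 1.24 | 84.3% |
| 40% | 77.8% | 84.0% | 1.30 | 65.8% |
| 30% | 80.8% | 86.7% | 1.40 | 46.3% |
| 20% | 87.3% | 92.0% | 1.60 | 29.1% |
| 10% | 96.1% | 98.1% | 2.20 | 15.2% |

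With 255 per arm, power for 12 points is lowest at 77.5%, near a 44% control rate, and rises as the rate falls further.

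**Step 3: the missing-data rule.** Suppose 50% and 62% are rates among women with a result, and 15% are missing in each arm. Over all randomized women the rates become 0.85 × 50% = 42.5% and 0.85 × 62% = 52.7%, a difference of 10.2 points. With n = 300 and p̄ = 0.476: (0.102 − 1.96 × 0.04078)/0.04057 = 0.544, so power is 70.7%.

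**Step 4: detectable effects on the analysis basis.** These use 300 per arm, 80% power, and control rates over all randomized women with missing as nonadherent.

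| Control rate (assumed) | Detectable difference | Detectable ratio |
|---|---|---|
| 10% | 7.9 points | 1.79 |
| 20% | 9.9 points | 1.49 |
| 30% | 10.9 points | 1.36 |
| 40% | 11.4 points | 1.28 |

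**The case against.** The strongest reply is that the protocol claims power for an absolute difference of 12 points, and that claim survives (Step 2). No section names a target ratio of 1.24. Reporting a relative risk does not create one, because a ratio of 1 and a difference of 0 are the same null hypothesis. This stands. A reader might infer that the trial is badly underpowered if adherence is low; the documents do not support that. The low power in the last column of Step 2 applies only if the effect is proportional and of the size 62/50.

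The pilot also cuts both ways. Its 22% comparison figure came with 42% under the intervention, a gap that 255 per arm would detect with 99.8% power. It is fair to answer that the pilot was nonrandomized, but that caveat applies to both of its figures.

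A reader might go further and multiply the article's percentages into a specific control rate, for example 22% × 55% = 12% (pilot persistence times high self-reported adherence), or 52% × 50% = 26% (detectable drug times continuation). Neither holds. The article does not say that the 55% applies to those who persisted, nor that the 52% came only from continuers, so the second product may count discontinuation twice. The article gives no time horizon for the 22%.

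On specimen type, Laboratory Procedures reports significant correlations between hair and blood-spot levels, which weakens that limb. Correlation does not, however, make the proportion above a daily-dosing cutoff equal to the proportion with any drug.

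On attrition, the 50% might be meant as the rate over all randomized women. No attrition deduction would then be needed, and power would be 84.3%. The paragraph does not say so, and deducting 15% implies the other reading.

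Table S2 may already list other control rates. The text nonetheless commits to 50% and gives a rationale that does not fit.

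**Conclusion.** The point holds as a misfit of the planning input, not as a miscalculation. The 50% rate is for a different and easier outcome, and its stated justification does not connect it to the primary endpoint. Discontinuation above 50% within 30 days and 22% persistence in the pilot comparison group suggest a lower rate, without fixing one.

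The consequence is moderate. The 12-point claim keeps roughly its stated power, but it would represent a larger relative effect than readers would assume. The mismatch between the attrition allowance and the missing-data rule lowers power to about 71%, if the planned rates refer to women with results and 15% are missing equally in both arms. The control rates used are an assumed range. This should be corrected, but it does not undermine the design or the sample size.

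**What to change.** Keep the sample size at 600. In the Sample Size section:

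1. Stop presenting the detectable-level rate as the control rate for this endpoint. Say plainly that no rate is available for hair tenofovir at the 0.038 ng/mg cutoff 6 months post partum, or cite one if it exists.
2. Restate detectability on the basis the analysis uses: 300 per arm, missing counted as nonadherent, no separate attrition deduction.
3. Give the detectable difference and ratio over a range of control rates, as in Step 4. If Table S2 already does this on the same basis, refer to it explicitly and align the text with it.

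The cost is one paragraph and possibly one table. No participants are added, and the endpoint, test and analysis do not change. The stated sensitivity will look less favorable on the relative scale.

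### The stated 80% power for a 12-point difference fits dropping the 15% lost, but the primary analysis counts them as nonadherent; under that rule power is about 71% or about 84%, depending on a scale the article does not state

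*Protocol article*

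**What the plan says.** Protocol article, Sample Size. The planning rate is given as "Assuming a PrEP adherence estimate of 50% in the SOC arm at 6 months post partum". It is drawn from earlier work in which "the frequency of detectable PrEP drug levels is approximately 50% among pregnant women who initiate PrEP in MCH clinics". With 600 women allocated 1:1, the claim is that "we will have 80% power to detect a minimum detectable difference of 12% between arms", "assuming 15% attrition and a 2-sided test with a Cronbach α of .05". I read the last figure as the two-sided significance level and the 12% as absolute percentage points, so the comparison is 50% with 62%. The section refers to Table S2 in the appendix, which is not shown.

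Protocol article, Statistical Methods and Analyses. The primary outcome "will be assessed in an intention-to-treat analysis comparing randomization arms mWACh-PrEP versus SOC", and "Missing primary outcomes or loss to follow-up will be assumed nonadherent".

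Protocol article, Background. The source cited for the 50% is also cited there. It is described as reporting detectable drug levels in 52% of pregnant women, in dried blood spots taken at follow-up visits.

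**The concern.** Attrition can enter a power calculation for a binary outcome in two ways. If women without an outcome are left out, the sample shrinks and the rates stay as they are. If they are kept and coded as failures, the sample stays whole, both rates fall, and so does the gap between them. The second usually costs more power for the same attrition. The analysis section fixes the second; the figures in the sample size section look like the first.

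If so, the stated power does not belong to the planned primary analysis. A true 12-point gain among women who can be measured would be missed about 29% of the time instead of 20%, and a null result would be read against a sensitivity that the trial did not have.

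**Working it through.** **Inputs.** SOC rate 0.50; mWACh rate 0.50 + 0.12 = 0.62; 300 per arm; attrition 15%; two-sided 0.05 (all from Sample Size). Missing or lost = nonadherent, analysed as randomized (Statistical Methods and Analyses).

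**Formula.** Two-proportion normal approximation with pooled null variance:

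power = Φ[(d − 1.96·s0)/s1], where d = p2 − p1, s0 = √(2·p̄(1 − p̄)/n), s1 = √((p1(1 − p1) + p2(1 − p2))/n) and p̄ = (p1 + p2)/2.

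**Step 1. Reproduce the plan's figure by dropping the lost.**
- n = 300 × 0.85 = 255 per arm, 0.50 vs 0.62, p̄ = 0.56.
- s0 = 0.0440, s1 = 0.0436.
- (0.12 − 0.0862)/0.0436 = 0.775, so power = 78.1% (unpooled variance 78.5%).
- Difference detectable at 80% power: 12.3 points, which rounds to 12.

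This is within two points of the stated 80% and uses the stated 15%.

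**Step 2. Apply the stated missing-data rule, taking 50% and 62% as rates among women measured.**
- Analysed rates: 0.50 × 0.85 = 0.425 and 0.62 × 0.85 = 0.527. The difference is 0.12 × 0.85 = 0.102.
- n = 300 per arm, p̄ = 0.476, s0 = 0.0408, s1 = 0.0406.
- (0.102 − 0.0799)/0.0406 = 0.544, so power = 70.7%.
- Difference detectable at 80% power: 11.4 points as analysed, or 11.4/0.85 = 13.4 points among women measured.
- For 80% power at 42.5% vs 52.7%: 376 per arm, 752 in all.

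Other formulas give much the same: unpooled 71.0%, log relative risk 70.0%, continuity-corrected 67.8%.

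**Step 3. Take 50% and 62% as already counting the missing as nonadherent.**
- n = 300 per arm, 0.50 vs 0.62, s0 = 0.0405, s1 = 0.0402.
- (0.12 − 0.0794)/0.0402 = 1.008, so power = 84.3%.
- Difference detectable at 80% power: 11.3 points.

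| Reading | n per arm | Rates | Power | Detectable difference at 80% power |
|---|---|---|---|---|
| Lost women dropped | 255 | 50% vs 62% | 78.1% | 12.3 points |
| Stated rule, inputs among women measured | 300 | 42.5% vs 52.7% | 70.7% | 13.4 points measured, 11.4 analysed |
| Stated rule, inputs already on the analysed scale | 300 | 50% vs 62% | 84.3% | 11.3 points |

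**Step 4. Sensitivity of the 70.7% to attrition.**
- Equal loss in both arms: 5% gives 80.1%, 10% gives 75.5%, 20% gives 65.8%.
- Unequal loss: SOC 15% with mWACh 10% gives 90.5%; SOC 10% with mWACh 15% gives 47.1%.

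**The case against.** The strongest reply is about scale. The text speaks of a difference between arms in the primary outcome, and that outcome is defined with the missing counted as nonadherent. Read literally, the 12 points are then the contrast as analysed. On that scale the trial does better than claimed: 84.3% power from 50%, and 83.8% even from 42.5% (42.5% vs 54.5%, 300 per arm). This stands as a possible reading. A reader might infer that the planned analysis is underpowered whatever was meant, and the document does not support that. But on this reading the 15% deduction has no place, so the power statement still needs rewriting.

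Second, dropping the lost women is an inference. The article does not say how the 15% was used, and another route comes close: a continuity-corrected test on all 300 per arm has a detectable difference of 11.7 points from 50%, which also rounds to 12. So it would be too strong to say that the stated figure arises only by exclusion. That route, however, ignores the attrition that the text says was assumed. Exclusion remains the more natural explanation.

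Third, a planner may have applied a rounded 50% to the whole arm, lost women included. The documents lean the other way, since the Background describes the source rate as coming from samples collected at follow-up visits, but they do not settle it.

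Fourth, 42.5% and 52.7% are not forecasts. They follow mechanically from the plan's 50%, which is a frequency of detectable drug, whereas the primary outcome uses a hair cutoff tied to daily dosing. This stands: the figures show what the plan's own inputs imply under its own rule, and no more.

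**Conclusion.** The point holds as an inconsistency between two adjacent sections. The combination of 12 points, 80% power and 15% attrition fits an analysis that drops the lost women, and the stated primary analysis does not drop them. Under the stated rule, the plan's inputs give about 71% power if they describe women measured, or about 84% if they already count the missing as nonadherent. The first reading is better supported because of where the 50% comes from.

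The 71% rests on three assumptions: the 50% and the 12 points are both on the scale of women measured, loss is 15%, and loss is equal in the two arms. It would be wrong to report 71% as the trial's power without them.

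The estimate and its confidence interval are unaffected. What is wrong is the sensitivity claimed for the primary test.

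**What to change.** Keep the 600 women and keep the rule that counts missing outcomes as nonadherent. In the Sample Size section, and in Table S2 if it used the same method:

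- State whether the 50% and the 12 points describe women with a measured outcome or all women randomized with the missing counted as nonadherent.
- If women measured: report that, with 15% loss in each arm, the stated inputs become 42.5% vs 52.7%, power is about 71%, and the difference detectable at 80% power is about 13.4 points among women measured (11.4 as analysed). Add that this assumes equal loss, and give about 75.5% at 10% loss and 66% at 20%.
- If all women randomized: remove the attrition deduction and report about 84% power, or about 11.3 points at 80% power.

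The cost is a rewritten sentence and, where needed, a recomputed table. Under the better-supported reading the stated figure becomes less favourable. No patients, visits or analyses are added.

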#### Statistical Methods and Analyses

The primary outcome, PrEP adherence at 6 months post partum, will be assessed in an intention-to-treat analysis comparing randomization arms mWACh-PrEP versus SOC. Enrollment characteristics will be compared between randomization arms to assess the balance between arms and control for any imbalanced factors. Based on a previous study of directly observed dosing conditions, we will use a hair TFV concentration cutoff of 0.038 ng/mg (corresponding to 7 doses/week) as the threshold of detection for the primary adherence outcome measured at 6 months post partum (detectable/nondetectable binary outcome) [52]. Protective PrEP drug level thresholds for cisgender women have not been established; however, current WHO and Kenyan national guidelines recommend daily (7 doses/week) oral PrEP for cisgender women. A log-binomial regression model will be used to estimate the relative risk, adjusting for any imbalances in baseline demographic, clinical, or behavioral characteristics between arms. Missing primary outcomes or loss to follow-up will be assumed nonadherent. To evaluate the sustained effect of mWACh-PrEP on PrEP-taking habits after the SMS text messaging intervention ends, the same model will be used to analyze our secondary outcome of PrEP adherence at 9 months post partum (3 months after cessation of mWACh-PrEP messaging).

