**Methods:**

The mWACh-PrEP study is a randomized trial designed to support PrEP adherence during the peripartum period by comparing mWACh-PrEP to the standard of care (ie, in-clinic adherence counseling) among women who are HIV negative and initiating PrEP. Purposive sampling was used to select 5 facilities offering PrEP in antenatal clinics in Kisumu and Siaya Counties, and block randomization will be used to divide participants into groups. Participants in the intervention arm will receive a customized messaging curriculum via SMS text messages targeted toward their particular perinatal stage. The primary outcome, PrEP adherence at 6 months post partum, will be evaluated using a log-binomial regression model, adjusting for imbalanced baseline characteristics. Based on a previous study of directly observed dosing conditions, we will use a hair tenofovir concentration cutoff of 0.038 ng/mg (corresponding to 7 doses/week) as the primary adherence outcome measured at 6 months post partum (binary outcome). Qualitative interviews and cost-effective analyses will be conducted to understand the feasibility, acceptability, and economic impact of the intervention.

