## Methods

### Study Design

We are conducting a nonblinded individual-level RCT comparing 2 arms of PrEP adherence to determine the effect of the mWACh-PrEP tool on PrEP adherence among pregnant women at risk for HIV acquisition initiating PrEP within ANC clinics.

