#### Randomization

Block randomization using a 1:1 allocation in random-sized blocks stratified by recruitment site is being used to ensure a balanced allocation of each arm within sites. Before randomization, study nurses ensure all routine PrEP initiation services and study enrollment procedures are complete. Treatment allocation (mWACh-PrEP or SOC) for each consented participant is done by the study nurses within the individual’s health facility using Research Electronic Data Capture (REDCap; Vanderbilt University). The randomization code is stored in an electronic format, and once assigned, it is unblinded. The randomization key for the database is restricted to the data manager and statistician.

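### The primary model adjusts for whichever baseline factors look imbalanced, not for site and a fixed prognostic list; this forgoes precision and leaves the model open until the arms are compared

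*Protocol article*

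**What the plan says.** Statistical Methods and Analyses gives the rule twice. It first says "Enrollment characteristics will be compared between randomization arms to assess the balance between arms and control for any imbalanced factors". It then describes the log-binomial model for the relative risk as "adjusting for any imbalances in baseline demographic, clinical, or behavioral characteristics between arms". The abstract (Methods) agrees: the primary outcome "will be evaluated using a log-binomial regression model, adjusting for imbalanced baseline characteristics". The same model is to be used for adherence at 9 months post partum.

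No covariate is named, and nothing is said about what counts as imbalanced. The Randomization section describes "Block randomization using a 1:1 allocation in random-sized blocks stratified by recruitment site", but site is not named as a term in the model. Enrollment Visit Data Collection lists a long set of candidates: demographic, pregnancy and medical history, mental health, risk perception, partner characteristics, PrEP attitudes, wealth, health literacy, partner violence, two depression scales and the HIV risk score.

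On who knows the allocation, Study Design says "We are conducting a nonblinded individual-level RCT comparing 2 arms of PrEP adherence", and Randomization says "The randomization key for the database is restricted to the data manager and statistician".

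**The concern.** In a properly randomised trial, a baseline difference between arms arises by chance. Adjustment pays when a covariate predicts the outcome, whether or not it is imbalanced. A rule keyed to imbalance selects on the wrong property: it can admit a factor unrelated to hair tenofovir and leave out a strong predictor that happens to be even.

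Site shows this most clearly. Blocked allocation within site makes a site imbalance unlikely, so the rule would rarely bring site in. Yet site is the one factor the design itself treats as important. If site predicts adherence, omitting it wastes the precision that stratification was meant to give.

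Two things are at stake: the precision of the primary relative risk, and whether the primary model is settled before anyone has compared the arms.

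**Working it through.** **1. The plan's own figure.** Inputs from Sample Size: 50% adherence under standard of care, a 12-point difference (62%), 600 women 1:1, 15% attrition, two-sided 0.05. Evaluable per arm: 300 × 0.85 = 255.

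Power = Φ[(Δ√n − 1.96√(2p̄(1−p̄))) / √(p₀(1−p₀) + p₁(1−p₁))], with p̄ = 0.56:

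- Δ√n = 0.12 × 15.969 = 1.916
- 1.96 × √0.4928 = 1.376
- √(0.2500 + 0.2356) = 0.697
- Φ[(1.916 − 1.376)/0.697] = Φ(0.775) = 78.1%

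The difference detectable at exactly 80% is 12.3 points, which rounds to the stated 12. The figure reproduces, and it comes from an unadjusted comparison of two proportions.

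**2. How often the rule would change the model.** With K independent factors each tested at 5%, the chance that at least one is flagged is 1 − 0.95^K: 40% for 10 factors, 64% for 20, 79% for 30.

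The criterion also matters. With 15 factors, p<0.05 selects 15 × 0.05 = 0.75 on average. A standardised difference above 0.1 has standard error √(2/300) = 0.082, so each factor is selected with probability 2[1 − Φ(1.22)] = 0.22, or about 3.3 of 15.

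**3. Power under the rule.** The article gives neither the number of factors nor their prognostic strength, so both are assumed. Simulation: 510 evaluable women, 50% v 62%, 10 independent binary baseline factors of which 2 or 3 are prognostic. Each prognostic factor moves risk up or down by the stated number of points. The model is log-link Poisson with robust variance, standing in for log-binomial. The imbalance rule is p<0.05. There were 6,000 trials per row (4,000 for the 20-factor row); Monte Carlo error is about 0.5 point per cell, and all analyses use the same trials.

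| Assumed prognostic factors | Unadjusted | Imbalance rule | Fixed prognostic set | Fixed minus rule |
|---|---|---|---|---|
| 3, ±3 points | 77.1% | 76.8% | 77.9% | 1.1 |
| 3, ±5 points | 77.7% | 77.8% | 79.6% | 1.8 |
| 3, ±10 points, run 1 | 77.7% | 78.0% | 82.9% | 4.9 |
| 3, ±10 points, run 2 | 76.3% | 76.7% | 82.1% | 5.4 |
| 2, ±15 points | 77.3% | 78.1% | 85.3% | 7.2 |
| 3, ±10 points, 20 factors | 77.2% | 77.8% | 82.6% | 4.8 |

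Differences are taken from the rounded figures. With 10 factors, the rule moves power by −0.3 to +0.8 points relative to no adjustment.

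The plan counts missing outcomes as nonadherent. Under 15% missing in both arms that gives 0.85 × 50% = 42.5% v 0.85 × 62% = 52.7% on all 600 women. With 3 factors at ±10 the gap is similar: 69.9% under the rule, 75.6% with the fixed set. The lower level there reflects the missing-outcome rule, a separate matter.

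**4. Type I error.** With equal arms at 50%, the rule applied mechanically rejects in 4.4% (10 factors, 3 at ±10), 4.2% (10 factors, 2 at ±15) and 4.1% (20 factors, 3 at ±10) of trials. There is no inflation.

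The simulation contains no site effect, so the table says nothing about what adjusting for site would add.

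**The case against.** The strongest reply is that this is a common convention with little proven harm. Selection uses enrolment data only, never outcomes. The outcome is a laboratory hair concentration with a fixed cutoff, so open allocation bears on this point only through the analyst's choice of model. A statistical analysis plan is mentioned (the external advisory panel reviews it) and may well set the criterion and the list. All of that stands, and the missing criterion is not counted as a fault here. What remains is the rule itself, which the article states and which selects on the wrong property.

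A reader might infer that the rule raises the error rate. It does so only if someone fits several models and reports the most favourable. The best of the unadjusted, fixed and imbalance-adjusted models rejects in 6.2 to 6.7% of null trials, but nothing in the article proposes that, and the stated rule on its own gives 4.1 to 4.4%.

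A reader might also blame the rule for possible failure of the log-binomial model to converge. That cannot be pinned on the rule: site (5 facilities, so 4 indicators) plus four covariates is 8 terms, usually more than the rule would select. It is instead a reason to choose a robust estimator when the covariates are fixed.

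Finally, the gain from fixed adjustment depends on covariates whose prognostic value the article does not show. Eligibility already narrows gestational age (24 to 32 weeks) and risk score (6 or above), and partner HIV status is not named among the enrolment variables. This is fair, and it is why the size is given as a range.

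**Conclusion.** The point holds as one of efficiency and pre-specification. Choosing covariates by observed imbalance brings almost no gain over an unadjusted analysis and forgoes about 1 to 7 points of power against a fixed prognostic set. The low end applies if baseline factors barely predict adherence, the high end if two of them predict it strongly. The range rests on the assumed number, independence and strength of the factors and on a p<0.05 criterion.

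It would be wrong to conclude that the stated 80% power fails because of this rule: that figure is unadjusted, and the rule leaves power about where an unadjusted test has it. Nor is there evidence that allocation knowledge has been or will be misused. Access to the randomization key only makes it more worthwhile to settle the model before the arms are compared. This is a free improvement, not a threat to the trial's validity.

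**What to change.** - Delete the imbalance rule in Statistical Methods and Analyses and in the abstract. If the analysis plan already fixes the covariates, bring the article into line with it.
- State that the primary model, and the same model at 9 months, adjusts for site plus a short list of enrolment variables whatever the observed balance. Draw the list from data already collected, choose it for expected prognostic value, and fix it before the primary analysis.
- Estimate the relative risk with a method that will fit those terms, such as Poisson regression with robust variance or logistic regression with marginal standardisation.
- Show baseline characteristics by arm descriptively. Report the unadjusted model and any imbalance-adjusted model as sensitivity analyses.

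Cost: one rewritten paragraph and a matching phrase in the abstract. No new data, no change to sample size and no change to participants' care.
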